In view of these doubts, the influence of different needling points and depths should be investigated. First, the acupoints of local lesions including *Jingbailao* (EX-HN 15) and *Jianzhongshu* (SI 15) are commonly used in our hospital for neck pain [15]. The analgesic mechanism of acupoints on local lesions has been established in the spinal segments control theory to explain the gate control theory [16, 17]. According to the innervations of the pain focus, the effects of stimulation of EX-HN 15 and SI 15 on neck analgesia will be studied for feasibility and repeatability [15]. Second, several different groups of non-acupoints and shallow punctures will be established to determine whether traditional acupuncture is more effective for chronic pain relief than sham acupuncture in adults with CNP. The different depth and placement of needle insertion will also be investigated to determine efficacy [18]. Third, a single-blinded practice will be used and the adequacy of subject blinding will also be carefully assessed. The patients will be advised to lie in the prone position on the treatment couch and will be unaware of the treatment course in this trial. Data collection will be completed by the researchers over a 3-month follow-up period. Finally, we will assess the pain threshold (PT) and pain diary as semi-objective outcomes to avoid subjective results.

In this research, a randomized clinical trial will be performed to determine whether the outcome of traditional acupuncture treatment is significantly different to sham acupuncture in relieving CNP. We also aim to investigate which type of sham acupuncture is the optimal control for clinical trials.

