### Interventions

Participants will be randomized to the five treatment groups and receive ten sessions of treatment over a period of 5 weeks. Acupuncture treatment will be performed by a senior acupuncturist who has held a practitioner licence for more than 10 years. The participants will be asked to rest for 15 min before treatment. A constant room temperature of 23 to 25 °C will be maintained to ensure the patients are comfortable and relaxed during treatment. Subjects will be advised to lie in the prone position on the treatment couch. Interventions will be performed twice a week from Monday to Friday. Each session will last for 20 min.

The combinations of EX-HN 15 and SI 15 will be selected for the different groups based on the academic literature [21]. EX-HN 15 is an acupoint on the neck, 2 cun (1 cun is equal to the width of the patient’s thumb knuckle stripe) above GV 14 (*Dazhui*), and 1 cun lateral to the posterior median line. SI 15 is located on the back, under the 7th cervical vertebra and 2 cun lateral to GV 14. According to TCM theory, stimulation of EX-HN 15 and SI 15 can remove meridian stasis by promoting the circulation of “Qi” and blood to relieve neck pain. After the skin is sterilized with disposable 75% alcohol swabs, a sterile needle (length: 25 mm, diameter: 0.30 mm; Huatuo, Suzhou Medical Supply Factory Co., Ltd., Suzhou, China) will be inserted. The needle-punching depth in the acupoint will be 0.5 to 0.8 cun. The needle will be manipulated by lifting and twirling until the participant feels a sensation (denominated *de-qi*).

The needle in the non-acupoint will be inserted without the use of acupuncture techniques during the experiments. Non-acupoints 1 and 2 are located 1 cm lateral to EX-HN 15 and SI 15. The shallow puncture is just enough to maintain the needles in a fixed position and not enough to produce *de-qi*. For subjects receiving sham puncture, “Streitberger” needles (Asiamed Inc., Bridport, UK) with blunt tips will be used in the same areas as those in the treatment group, but will not pierce the skin. The needles will then be fixed and retained for 20 min. The treatment details in each group are illustrated in Table 1.

**Table 1 Tab1:** Treatment details of each group

Group	Acupoint	Manipulation
Group A traditional acupuncture	EX-HN 15 (*Jingbailao*)	The needle-punching depth in the each acupoint is 0.5 to 0.8 cun. The sensation (denominated *de-qi*) is necessary
	SI 15 (*Jianzhongshu*)	

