Group B acupoints shallow puncture	EX-HN 15 (*Jingbailao*)	The needles are pierced through the skin for 0.2 cun and not enough to produce *de-qi*
	SI 15 (*Jianzhongshu*)	
Group C non-acupoint acupuncture	Non-acupoint 1	The needle-punching depth in the acupoints is 0.5 to 0.8 cun. The sensation (denominated *de-qi*) is necessary
	Non-acupoint 2	
Group D non-acupoint shallow puncture	Non-acupoint 1	The needles are pierced through the skin for 0.2 cun and not enough to produce *de-qi*
	Non-acupoint 2	
Group E sham puncture	EX-HN 15 (*Jingbailao*)	The placebo needle tip is pressed and fixed on the skin of the acupoint
	SI 15 (*Jianzhongshu*)	

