Clinical trials of traditional acupuncture for chronic pain, with optimal control groups, are rare, with the exception of the use of standard outcome measures and rigorous blinding of participants to treatment assignment [38]. However, few guidelines exist for conducting appropriate sham acupuncture, for the depth of the inserted needle or the parameter for needle stimulus [39, 40]. This randomized placebo-controlled trial addresses the urgent need to provide evidence-based control groups for adults with CNP and to determine the evidence for the specificity of acupoints. At the end of this clinical trial, we expect that the findings will provide evidence to answer the question: is acupuncture more effective than a placebo?

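### At the acupoints, needle depth changes only together with manipulation and de-qi, so a difference between groups A and B cannot be attributed to depth

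*Protocol article*

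**What the plan says.** The Background names depth twice as something to be studied. It gives the motive, "the influence of different needling points and depths should be investigated", and then the intention: "The different depth and placement of needle insertion will also be investigated to determine efficacy".

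The arms are defined under Interventions and in Table 1:

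- **Group A (acupoints, deep).** Table 1: "The needle-punching depth in the each acupoint is 0.5 to 0.8 cun", with de-qi marked as necessary. The text adds the technique: "The needle will be manipulated by lifting and twirling until the participant feels a sensation".
- **Group B (acupoints, shallow) and group D (non-acupoints, shallow).** Table 1: "The needles are pierced through the skin for 0.2 cun and not enough to produce" de-qi. The text defines the procedure in the same way: "The shallow puncture is just enough to maintain the needles in a fixed position and not enough to produce" de-qi.
- **Group C (non-acupoints, deep).** Table 1: "The needle-punching depth in the acupoints is 0.5 to 0.8 cun", again with de-qi marked as necessary. The Interventions text says instead that needling at non-acupoints involves no acupuncture technique.
- **Group E.** A blunt needle at the acupoints that does not pierce the skin.

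The aims in the Abstract and in the last paragraph of the Background are traditional versus sham acupuncture, and which sham is the best control.

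**The concern.** A reader of the Background would expect the trial to say something about depth, and would look for it in A versus B, which share the same points. Those arms differ in three respects: depth, needle manipulation and de-qi. If A did better than B, stimulation could be the reason, or depth, or both. If A and B came out alike, that would not show that depth is irrelevant either, because opposing effects could cancel. Any published statement on depth at the acupoints would go beyond what the arms support. No analysis method can repair this, because the missing contrast is a matter of which arms exist.

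**Working it through.** The plan gives no figure for this point, so there is none to reproduce. The check is whether the arms allow a depth effect to be separated from stimulation.

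**Inputs** (Interventions text and Table 1; 35 patients per group from Sample size calculation). Code placement as 1 for acupoint, depth as 1 for 0.5 to 0.8 cun, and stimulation as 1 where de-qi is required. For group A the text also describes lifting and twirling.

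**Reading 1: Table 1 governs group C.**

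| Group | Intercept | Placement | Depth | Stimulation |
|---|---|---|---|---|
| A | 1 | 1 | 1 | 1 |
| B | 1 | 1 | 0 | 0 |
| C | 1 | 0 | 1 | 1 |
| D | 1 | 0 | 0 | 0 |

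The depth and stimulation columns are identical (1, 0, 1, 0), so the matrix has rank 3 with 4 columns. In an additive model:

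- A − B = depth + stimulation
- C − D = depth + stimulation

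Only the sum can be estimated. This covers all four penetrating arms, 4 × 35 = 140 of 175 planned patients. Adding group E together with a column for skin penetration gives rank 4 of 5, so the non-penetrating arm does not separate the two.

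**Reading 2: the Interventions text governs group C (no technique, taken here to mean no de-qi).** Row C becomes (1, 0, 1, 0) and the matrix has rank 4 of 4. Then:

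- A − B = depth + stimulation, still mixed
- C − D = depth, at non-acupoints only
- A − C = placement + stimulation, now mixed as well

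Depth at the acupoints could then be obtained only by borrowing the C-versus-D estimate, on the assumption that depth acts equally at both placements.

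**Result.** A versus B (2 × 35 = 70 patients) mixes depth and stimulation under both readings. C versus D mixes them under Table 1 and would separate depth only under the second reading. Sample size plays no part in this.

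**The case against.** The strongest reply is that the protocol never promises an isolated depth effect. The formal aims do not name one, the Background sentence introduces the set of sham arms, and shallow puncture is openly defined as a procedure without de-qi. On that view the package is already what is being compared. The statistical section plans a general analysis of variance and no depth contrast.

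Much of this stands, and it limits the point. Three stronger readings that a reader might infer are not supported:

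- **That the trial cannot inform on depth anywhere.** If the Interventions text governs group C, C versus D could isolate depth at non-acupoints.
- **That the Discussion commits the trial to estimating depth and stimulus separately.** It says that few guidelines exist "for the depth of the inserted needle or the parameter for needle stimulus". That describes a gap in guidance and is not an objective.
- **That the search for the best sham is undermined.** That aim compares whole procedures with group A. Whether B is a suitable sham as defined can be judged without knowing which component is responsible.

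The reply does not remove the Background wording. It presents depth twice as something to be investigated, the second time to determine efficacy, and does not say there that depth changes along with stimulation. The text also describes lifting and twirling as an action of the operator, so the difference between A and B is not simply a by-product of depth.

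**Conclusion.** The point holds for A versus B: a difference between these groups cannot be attributed to depth, whichever way group C is settled. For C versus D it holds if Table 1 governs. The contradiction between Table 1 and the Interventions text on group C must be reconciled before that contrast can be interpreted.

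As to size, the share of an A-versus-B difference that is due to depth is not estimable from that contrast. It is tempting to say that it lies somewhere between none and all of the difference, but that is not a valid bound: if depth and stimulation acted in opposite directions, the share could fall outside it.

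The conclusion rests on the arm definitions as printed, and on treating manipulation and de-qi together as one stimulation component. The main comparison of traditional with sham acupuncture and the ranking of shams as delivered are intact. This is a limit on interpretation and leaves the design usable.

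**What to change.** Keep all five arms.

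1. In the Background, replace the general statement on depth with the contrast that the arms provide: A versus B compares deep needling with manipulation and de-qi against shallow insertion without either.
2. State that no conclusion on depth alone will be drawn from A versus B.
3. Reconcile the Interventions text with Table 1 on how group C is needled. Which of the two is right is for the investigators to say.
4. State that C versus D will likewise support no conclusion on depth alone, unless the reconciled text shows that C and D differ only in depth. Even then the conclusion would apply to non-acupoints.

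Items 1, 2 and 4 are wording only and change no arm, endpoint, sample size or test. Item 3 needs the investigators to settle which description applies. The price is a narrower claim about depth.

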## Methods/design

### Study design

A single-center randomized controlled trial (RCT) has been designed to compare the differences between traditional acupuncture and sham acupuncture in patients with CNP. In total, 175 patients with CNP will be enrolled. According to the study plan, patients will receive ten treatments over 5 weeks. This trial will be conducted in Guangdong Provincial Hospital of Chinese Medicine from August 2015 to December 2017. The study design is shown in the flowchart in Fig. 1, and the study schedule is presented in Fig. 2.

**Fig. 1 Fig1:**
[figure not shown]
Flowchart of the study design. A total of 175 participants will be randomized to the five groups. The interventions will last for 20 min and will be carried out twice a week for 5 weeks. The study period will be consisted of the baseline, 5 weeks of treatment, and 3-month follow-up

**Fig. 2 Fig2:**
[figure not shown]
Study schedule. Study protocols on enrollment and time points for assessments using the Standard Protocol Items: Recommendations for Interventional Trials (SPIRIT) figure. W3: the 5th treatment during the 3rd week, W5: the 10th treatment during the 5th week

### Recruitment

The participants will be recruited by bulletin board advertisements in the Traditional Chinese Medicine Hospital of Guangdong Province. Recruitment staff in the acupuncture clinic will be responsible for the enrollment of participants. If a patient with CNP meets the study criteria, they will be invited to the clinical research center to undergo examination. The screening process will last for 1 week, and will require each participant to record their symptoms in a diary without treatment during this period. Recruitment is expected to occur from August 2015 to July 2017.

### Eligibility criteria

Patients meeting the following criteria will be selected as study volunteers. The inclusion criteria for this study will include: (1) men and women aged 18 to 60 years, (2) patients with neck pain as the main symptom for at least 3 months, (3) episodes of pain lasting for over 30 min, and frequency of pain occurring at least once per month, (4) a score of 3 or more on the Visual Analogue Scale (VAS) for perceived pain intensity, (5) no acupuncture therapy within 3 months prior to study recruitment and (6) willing to participate in the study and be randomly allocated into study groups.

### Exclusion criteria

Participants meeting one of the following criteria will be excluded: (1) history of cervical intervertebral disc herniation accompanied by nerve symptoms, neck trauma or have a surgical neck fracture, spinal disease or infectious inflammatory autoimmune diseases, congenital vertebral anomalies, or compression fractures, (2) any other conditions including active skin infection, clotting disorders, administration of an anticoagulant agent, pregnancy and seizure disorders, (3) other chronic diseases including liver or kidney disease, cerebrovascular disease, leukemia, thrombocytopenia with bleeding tendency, or severe osteoporosis, (4) a severe psychiatric or psychological disorder related to severe neurosis, dementia and unable to communicate or provide self-care and (5) having taken corticosteroids, narcotics, muscle relaxants or herbal medicines to treat neck pain or any medication considered inappropriate by the recruitment investigators.

### Randomization and allocation concealment

The patients will be divided into five groups: a traditional acupuncture group (group A), a shallow-puncture group (group B), a non-acupoint acupuncture group (group C), a non-acupoint shallow-puncture group (group D) and a sham-puncture group (group E). Before randomization, all participants will be informed that they will be allocated into one of the above groups in an equal ratio, using block randomization with a block size of 5, and 35 participants are planned for each group. Randomization will occur on the second visit to the clinical research center according to the sequence generated by PEMS (Package for Encyclopedia of Medical Statistics) 3.1 software (West China School of Public Health, Sichuan, China) and overseen by an independent statistician. Randomization information will be sealed in opaque envelopes. If participants pass the screening test, a random number will be assigned sequentially.

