### Blinding

All patients will be treated in the acupuncture clinical research center and will not be informed of the type of treatment that they will receive. Outcome assessors, data managers and the statistician will be blinded in this trial. To preserve masking, only the acupuncturists will have access to treatment allocation [19, 20]. However, they must learn how to use the blinding method to communicate with participants to ensure treatment blinding. The blinding principle will be operated until the data are locked down. The questionnaires regarding blinding will be completed immediately after the 5th and 10th treatments, as well as at the end of the follow-up. The success of these blinding strategies will be appraised at the end of the study by the Blinding Index (BI).

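### A single fixed block size of 5 for five equal arms makes allocations easy to deduce from past ones, an avoidable opening for selection bias

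*Protocol article*

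**What the plan says.** The section on randomization and allocation concealment in the protocol article states that "The patients will be divided into five groups" and that allocation is in equal ratio, "using block randomization with a block size of 5, and 35 participants are planned for each group". The sequence is software-generated and overseen by an independent statistician. It is kept in sealed opaque envelopes, and numbers are assigned in order once screening is passed. Randomization takes place at the second visit to the clinical research center.

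The Study design section says: "A single-center randomized controlled trial (RCT) has been designed". No stratification factor is given.

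On who knows what, the Blinding section says "only the acupuncturists will have access to treatment allocation", while outcome assessors, data managers and the statistician are blinded. On who enrols, the Recruitment section says: "Recruitment staff in the acupuncture clinic will be responsible for the enrollment of participants". The exclusion criteria leave one item to judgement at entry: "any medication considered inappropriate by the recruitment investigators".

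Nothing in the article varies the block size, withholds it from site staff, or states that enrolment is kept apart from the unblinded acupuncturists.

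**The concern.** Concealment needs two things: nobody can read the next allocation, and nobody can work it out. Opaque envelopes deal with the first. They do nothing for the second, because the information lies in the allocations already made. With one permutation of the five arms per block, that information accumulates quickly, and the acupuncturists hold it as a by-product of delivering treatment.

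If it reached whoever decides on entry or on the timing of the randomization visit, a patient expected to respond well or badly could be steered towards or away from a particular allocation. That would undermine the comparison of traditional acupuncture with the sham arms. Blinded assessment does not help, since the selection would happen before allocation, and an analysis cannot reliably correct for it afterwards.

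**Working it through.** **Inputs.** Five arms, equal ratio, block size 5 and 35 per group (randomization section); 175 patients in total (Fig. 1 legend: "A total of 175 participants will be randomized to the five groups"); one centre (Study design). One running list is an assumption, made because no stratification is stated.

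**The plan's own figure.** 5 × 35 = 175, and 175 / 5 = 35 complete blocks. The stated total is reproduced.

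**Predictability with blocks of 5.** Each block is one permutation of A to E. An observer who knows the block boundary and the earlier allocations in the block has 6 − j arms left at position j, so the chance of a correct guess is 1/(6 − j):

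| Position in block | 1 | 2 | 3 | 4 | 5 |
|---|---|---|---|---|---|
| Chance of a correct guess | 20% | 25% | 33% | 50% | 100% |

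- Mean: (1/5 + 1/4 + 1/3 + 1/2 + 1) / 5 = 0.457, or 0.457 × 175 ≈ 79.9 correct guesses. Chance alone gives 175 / 5 = 35 (20%).
- Certain allocations: one per block, 35 of 175 = 20%. A further 35, the fourth in each block, are a one-in-two guess.

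**For group A against any control arm.** Once A has appeared in a block, every later patient in it is known to be a control. A is equally likely at each position, so the expected number of later patients is (4 + 3 + 2 + 1 + 0) / 5 = 2 of 5 (40%). In one block in five A comes last and is itself known, adding 0.2 of 5 (4%). The observer therefore knows whether the next patient is in A or in a control arm for 2.2 / 5 = 44% of allocations, 77 of 175.

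**Alternatives (simulation, 175 patients).** When block sizes are unknown, the natural strategy is to guess the arm used least so far:

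| Random block sizes | Correct guesses |
|---|---|
| 5, 10, 15 | about 40% |
| 10, 15, 20 | about 37% |
| 25, 35 | about 33% |

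If the observer knows the set of sizes but not their order, some allocations remain certain: 3.2% with 5/10/15 and 4.0% with 10/15, against 20% now.

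**Price in balance.** With blocks of 10, 15 and 20 stopped at 175 patients, the gap between the largest and smallest arm averaged 1.3 patients, with a maximum of 4 in 4,000 runs.

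**The case against.** The strongest reply is that knowledge and enrolment sit with different people. The Blinding section restricts access to allocation to the acupuncturists, and the Recruitment section gives enrolment to recruitment staff. Read together, recruiters do not see allocations. This stands as far as it goes, and it is why the point must be conditional. It does not dispose of it: the recruiters work in the acupuncture clinic, and no separation from the treating acupuncturists is stated.

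A second reply is timing. A one-week screening period with a diary precedes randomization at the second visit, so a decision made at first contact comes before the patient's place in the sequence is fixed. That limits exploitation but does not exclude it, because the second visit can be scheduled and eligibility keeps an element of judgement.

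Third, the plan has real safeguards: a software-generated sequence, an independent statistician, opaque envelopes, sequential assignment and blinded assessors. They guard against reading ahead and against biased assessment. None guards against deduction.

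Two stronger readings are tempting, and neither is supported:

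- A reader might infer that allocation is in fact subverted and the comparison biased. The figures above measure how guessable the list is. They give neither direction nor size of any bias in the neck pain score.
- A reader might also make much of disclosure to patients, since the sentence beginning "all participants will be informed that they will be allocated into one of the above groups in an equal ratio" runs on to the block size. It can equally be read as informing them of the ratio only, with the block size describing the method. Even on the literal reading, blinded patients do not know one another's allocations and can predict nothing. The point rests on the block size being fixed and printed in the protocol.

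**Conclusion.** The point holds as a design weakness. A fixed block equal to the number of arms is the most predictable block that five equal arms allow, and here it is combined with one centre and providers who know every allocation. For a person with the necessary knowledge, 20% of allocations are certain and the average guess is right 45.7% of the time, against 20% by chance.

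This rests on three assumptions: a single running list; an observer who knows the block size, the block boundaries and all earlier allocations in the block; and, for any harm to follow, that this knowledge reaches someone who influences entry or its timing. The article supports the second for the acupuncturists. On the third it is silent in both directions. The arithmetic is certain; the existence of bias is not shown. The change is worth making because it is cheap and narrows the opportunity.

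**What to change.** For all patients not yet randomised, the independent statistician should issue a new list with randomly varying larger blocks, for example 10, 15 and 20. Both the sizes and the set from which they are drawn should be withheld from recruiters and acupuncturists, and not published until recruitment ends. The protocol should then say only that blocks of varying, undisclosed size are used. It would help to add a sentence stating whether the treating acupuncturists have any part in enrolment.

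The gain is real but partial. The best-guess rate falls from 45.7% to about 37%, still above the 20% of pure chance. Certain allocations largely disappear, though a few percent would remain if the set of sizes became known.

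The cost is a short amendment, a new set of envelopes and final arm sizes that may differ by a few patients, which matters little at about 35 per arm. Patients already randomised keep their allocation; the final report should state when the list changed.
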